#### **4.2.6 Visit 6 (telephone visit, 2 ~ 5 days after the 2nd dose)**

This visit will take place to the subject between 2 days and 5 days after the 2nd dose of the IP via phone call made by a trained sub-investigator.

- Any AEs and any change in concomitant medications since the last visit will be checked.
- The subject will be instructed to record any solicited and unsolicited AEs.
- The next visit day will be scheduled.

#### **4.2.7 Visit 7 (interim visit for the main study, 7 + 3 days after the 2nd dose)**

This visit will take place on Day 7 after the 2nd dose of the IP. Procedures to be carried out during this visit are as follows.

- Any change from the last visit in concomitant medications will be checked.
- The subject diary will be retrieved for status and details of AEs.
- Vital signs will be measured.
- Physical examination will be conducted.

- Clinical laboratory tests (hematology, blood chemistry, urinalysis) will be performed.
- The subject will be given a subject diary and instructions on how to complete the diary.
- The next visit day will be scheduled.

#### **4.2.8 Visit 8 (interim visit for the main study, 21 + 5 days after the 2nd dose)**

This visit will take place on Day 21 after the 2nd dose of the IP. Procedures to be carried out during this visit are as follows.

- Any change from the last visit in concomitant medications will be checked.
- The subject diary will be retrieved for status and details of AEs.
- Vital signs will be measured.
- Physical examination will be conducted.
- A blood sample will be collected for immunogenicity testing.
- The subject will be given a subject diary and instructions on how to complete the diary.
- The next visit day will be scheduled.

#### **4.2.9 Visit 9 (end of main study visit, 28 + 7 days after the 2nd dose)**

This visit will take place on Day 28 after the 2nd dose of the IP. Procedures to be carried out during this visit are as follows. The following procedures are also applicable to those who discontinue the study prior to Visit 9. Subsequently, if consent is obtained from the subject, telephone visits will be conducted by a trained sub-investigator who will call the subject at the time points of Visit 10 (Week 26 after the 2nd dose of the IP) and Visit 11 (Week 52 after the 2nd dose of the IP) for serious ADRs (SADRs) and AEs of special interest (AESIs).

- Any change from the last visit in concomitant medications will be checked.
- The subject diary will be retrieved for status and details of AEs.
- Vital signs will be measured.
- Physical examination will be conducted.
- Clinical laboratory tests (hematology, blood chemistry, urinalysis) will be performed.
- Pregnancy test will be performed for women of childbearing potential.
- The next visit day will be scheduled.

**4.2.10 Visit 10 (interim visit for follow-up, 26 ± 2 weeks after the 2nd dose)**

This visit will take place at Week 26 after the 2nd dose of the IP. Procedures to be carried out during this visit are as follows.

- Any SAEs and AESIs since last visit will be checked. If the subject experienced SAEs and AESIs, concomitant medications given for these events will also be documented.
- Vital signs will be measured.
- A blood sample will be collected for immunogenicity testing.
- The next visit day will be scheduled.

**4.2.11 Visit 11 (end of follow-up visit, 52 ± 4 weeks after the 2nd dose)**

As the final study visit, this visit will take place at Week 52 after the 2nd dose of the IP. Those who are withdrawn after Visit 9 will perform the following procedures except for blood sampling for immunogenicity testing, and if consent is obtained from the subject, telephone visits may be conducted by a trained sub-investigator who will call the subject at the time points of Visit 10 (Week 26 after the 2nd dose of the IP) and Visit 11 (Week 52 after the 2nd dose of the IP) for SAEs and AESIs.

- Any SAEs and AESIs since last visit will be checked. If the subject experienced SAEs and AESIs, concomitant medications given for these events will also be documented.
- Vital signs will be measured.
- Pregnancy test will be performed for women of childbearing potential.
- A blood sample will be collected for immunogenicity testing.

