## 7.2 Endpoints

### 7.2.1 Safety endpoints

- AEs
  - ① Immediate AEs occurring within 30 minutes after each IP dosing
  - ② Solicited local and systemic AEs occurring for 7 days (Day 0~ Day 6) after each IP dosing
    - ✓ Local AEs : pain, tenderness, erythema/redness, induration/swelling, itchiness
    - ✓ Systemic AEs : fever, fatigue/malaise, chills/rigors, headache, myalgia, joint pain, diarrhea, vomiting, abdominal pain, mucocutaneous reaction/rash, cough, acute bronchospasm, respiratory distress
  - ③ Unsolicited AEs occurring within 28 days after the last IP dosing
  - ④ SAEs occurring within 52 weeks after the last IP dosing
  - ⑤ AESIs occurring within 52 weeks after the last IP dosing
- Clinical laboratory tests (hematology/blood chemistry, urinalysis)
- Vital signs
- Physical examination

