#### **7.3.4.1 Adverse events**

Summary descriptions will be provided as below for details of treatment emergent AEs (TEAEs).

Frequency, incidence, and number of events will be presented for solicited local and systemic AEs observed for 7 days (Day 0~Day 6) after each IP dosing, immediate AEs (anaphylaxis related) occurring within 30 minutes after each IP dosing, and unsolicited AEs occurring within 28 days after the last IP dosing. By treatment group, type of AEs will be classified by severity, causal relationship, outcome, etc., and frequency, incidence, and number of events will be presented by category.

Additionally, frequency, incidence, and number of events will be presented for SAEs and AESIs collected within 52 weeks after the 2nd dose of the IP.

All AEs except for solicited local and systemic AEs will be classified by system organ class and preferred term of Medical Dictionary for Regulatory Activities.

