### **7.3.7 Planned interim analysis and safety monitoring**

Upon completion of data collection from all subjects in Part A up to Day 28 after the 2nd dose of the IP (end of main study, Visit 9), DB lock will be carried out for a data analysis based on which interim study results will be presented.

Also, upon completion of data collection from all subjects in Part A up to Week 26 after the 2nd dose of the IP (Visit 10), DB lock will be carried out on those collected data and the interim study results will be presented.

The data from all subjects in Part B up to Day 28 (end of main study, Visit 9) will be collected and DB lock on these data will be carried out for a data analysis. The interim study results will be presented.

Subsequently, once all subjects in Part A and Part B complete the study (end of follow-up, Visit 11), DB lock will be carried out, and the final results will be presented.

For the purpose of safety monitoring, the principal investigator will serve as the protocol safety manager based on the level of risk involved in this study. During the study period, the principal investigator will monitor according to the protocol the safety of subjects participating in the study at the applicable institution.

Whenever an SAE and/or an ADR occurs, the principal investigator will collect and review the data of the relevant subject as well as relevant safety information. In the event of an AE, unexpected issue, or a protocol non-compliance, the principal investigator will report to the sponsor (including the CRO), the IRB, and if necessary, the Ministry of Food and Drug Safety (MFDS) according to the protocol, the IRB-specific regulations, Good Clinical Practice (GCP), and other applicable regulations. In addition, if efficacy and safety information that might have a significant impact on the continuation of the study according to Section 9.11. 'Early termination or suspension of the study' in the protocol becomes known, the principal investigator will report to the sponsor in a timely manner, and in turn, the sponsor will discuss and decide on study continuation according to the sponsor's SOP.

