## 8.2 Collection and documentation of adverse events

- During the study, AEs will be collected from after the 1st dose (Visit 2) to Day 28 after the 2nd dose of the IP (Visit 9). All medical events occurring before the 1st dose of the IP will be documented as medical history.
- SAEs and AESIs will be collected from after the 1st dose (Visit 2) of the IP to the end of follow-up (Visit 11).
- Once AEs grade  $\geq 3$  are occurred during the course of 1st dose (Visit 2) to the end of follow-up (Visit 11), subjects should inform study institution or investigator through telephone call with reference to severity assessment of adverse events in subject diary, and investigator should primarily check symptoms via telephone call. Subjects who requires treatment of AEs by investigator will perform unscheduled visit for treatment with medication.
- Subjects who have the symptoms of COVID-19 infection such as fever or respiratory symptoms should inform investigator about their symptoms as followed by COVID-19 guidelines of Central Disease Control Headquarters·Central Disaster Management Headquarters, and will be instructed to visit study institution to be treated, observed and assessed. Investigator or study coordinator should follow up the AEs in subjects who are not available to visit study institution via telephone call.
- An AE report should include the following information: term of AE, duration (date of onset and date of resolution), severity, causal relationship to the IP, action taken for the IP, outcome, corrective treatment for the AE, and status of immediate AE/SAE.
- The investigator should document AEs as comprehensive diagnostic terms or symptoms using standard medical terminology rather than recording individual symptoms or signs.
- AEs occurring during the study should be followed up until the event is resolved or stabilized or the subject is lost to follow-up. Follow-up of AEs of which date of resolution is unknown as of Day 28 after the 2nd dose (Visit 6) will be determined at the discretion of the investigator.
- AEs occurring after the end of follow-up (Visit 11) will spontaneously be reported by subjects; if a subject reports to the investigator an AE that is considered to be an SADR, the investigator will report to the sponsor.

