#### **8.4 Reporting serious adverse events**

All SAEs occurring from after the 1st dose of the IP (Visit 2) to the end of study (Visit 11) should be reported, regardless of relationship to the IP, to the sponsor via telephone/fax/email within 24 days from when the event is known to the investigator and to the IRB at the institution within the period defined by the IRB.

AEs occurring after the end of study (Visit 11) will spontaneously be reported by subjects; the investigator will report to the sponsor only serious events that are related to the IP.

To protect subject privacy, the investigator should report SAEs to the sponsor using subject identification codes instead of personal information such as the subject's name, resident registration number, and address. If copies of some medical records are required, personal information except for the identification code will be blocked.

If the investigator obtains additional information about the reported SAE, he/she should submit a follow-up report. The investigator should follow up the SAE on a regular basis until the event is resolved or stabilized or the subject is lost to follow-up and should report to the sponsor and the IRB.

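### SAE and AESI collection ends at Visit 11, which may be held from Week 48, so the 52-week SAE and AESI endpoints can be observed up to 28 days short

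*Protocol*

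**What the plan says.** - **Endpoint (Protocol 7.2.1).** The two long-term safety endpoints are "SAEs occurring within 52 weeks after the last IP dosing" and "AESIs occurring within 52 weeks after the last IP dosing".
- **Analysis (7.3.4.1).** The period has the same length but is counted from the second dose: "frequency, incidence, and number of events will be presented for SAEs and AESIs collected within 52 weeks after the" second dose.
- **Last visit (4.2.11).** "As the final study visit, this visit will take place at Week 52" after the second dose, but its heading allows a range: "end of follow-up visit, 52 ± 4 weeks after the" second dose. The Schedule of Assessments and Section 3.1 give the same ±4 weeks.
- **End of collection (8.2).** SAEs and AESIs are collected from the first dose "of the IP to the end of follow-up (Visit 11"). The instruction that subjects telephone the site about Grade 3 or higher events also stops at Visit 11.
- **After Visit 11 (8.2, 8.4).** Reporting depends on the subject coming forward, and "the investigator will report to the sponsor only serious events that are related to the IP".
- **Final lock (7.3.7).** "once all subjects in Part A and Part B complete the study (end of follow-up, Visit 11), DB lock will be carried out".
- **Subjects without a second dose (Schedule of Assessments, note 11).** Visits 10 and 11 are timed from the date on which the second dose was scheduled.

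**The concern.** The endpoint period has a fixed length, but the collection period ends on a visit date that may fall up to four weeks earlier. Between an early Visit 11 and Day 364, an SAE judged unrelated, or an AESI that is not serious, belongs to the endpoint and has no collection route. The loss runs one way. A subject seen at Week 56 is observed for longer, but events after Week 52 lie outside the endpoint and cannot make up for what is missed in early attenders.

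The rest of the schedule avoids this. The on-site main-study visits after the first dose (Visits 4, 5, 7, 8 and 9) have plus-only windows, so the 28-day adverse event period is never cut short by a permitted visit date. Visit 10 also has a ± window, but there it does no harm, because Visit 11 asks about events since the previous visit. Nothing follows Visit 11.

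At stake is the completeness of long-term safety data in a first-in-human vaccine study, where safety is the primary objective of Part A and a secondary objective of Part B. A SAP cannot repair this, since events that were never collected cannot be analysed.

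**Working it through.** **Inputs from the protocol**
- Endpoint period: 52 weeks = 52 × 7 = 364 days after the last dose (7.2.1).
- Visit 11 window: 52 ± 4 weeks after the second dose (4.2.11).
- Planned subjects: 50 in Part A + 230 in Part B = 280 (7.1.1).
- Second dose scheduled at Day 21, window +5 days (4.2.5).

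**Step 1: two-dose subjects.** Earliest Visit 11 = 48 × 7 = Day 336; latest = 56 × 7 = Day 392. Guaranteed observation is 336 days against 364. Maximum shortfall = 364 − 336 = 28 days, and 28/364 = 7.7%. The stated 52 weeks is reached only if Visit 11 falls on or after Day 364.

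**Step 2: subjects without a second dose.** Their last dose is the first one, but Visit 11 is timed from the scheduled second-dose date. Earliest Visit 11 = 336 + 21 = Day 357 after the only dose, a shortfall of at most 364 − 357 = 7 days. If the scheduled date is taken as Day 26, it is 364 − (336 + 26) = 2 days.

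**Step 3: exposure lost over the trial.** The protocol does not say how visit dates will be spread, so the distributions below are assumptions. All 280 subjects are treated as two-dose completers. With T the week of Visit 11, weeks lost per subject = E[max(0, 52 − T)]. Planned exposure = 280 × 52 = 14,560 subject-weeks.

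| Assumed spread of Visit 11 | Seen early | Mean weeks lost per subject | Subject-weeks lost | Share of 14,560 |
|---|---|---|---|---|
| Uniform, Week 48 to 56 | 50% | ∫₀⁴ x/8 dx = 1.00 | 280 | 1.9% |
| 30% exactly at Week 52, rest uniform | 35% | 0.7 × 1.00 = 0.70 | 196 | 1.3% |
| Triangular, peak at Week 52 | 50% | ∫₀⁴ x(4 − x)/16 dx = 0.67 | 187 | 1.3% |
| Normal, SD 1 week | 50% | 1/√(2π) = 0.40 | 112 | 0.8% |

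Upper bound, everyone seen at Week 48: 280 × 4 = 1,120 subject-weeks, 7.7%.

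Counting the uniform case in whole days gives much the same answer: 28 of the 57 permitted days fall before Day 364 (49%), and the mean shortfall is (1 + 2 + … + 28)/57 = 406/57 = 7.1 days.

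**Step 4: does the lock cause the loss?** No. There is one final lock, after the last subject's Visit 11. Part B starts only after the safety review of all Part A subjects to Day 28 after their second dose. The earliest Visit 11 of a Part B subject who follows the dosing schedule therefore comes at least 28 + 21 + 336 = 385 days after any Part A second dose, and by then Part A has passed Day 364. The database is still open when most early attenders reach Week 52. What is missing is a contact to collect the data.

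**The case against.** The strongest reply is that this is an ordinary visit tolerance with a negligible effect. The visit is set at Week 52, and ±4 weeks only allows for scheduling. Related serious events can still reach the sponsor after Visit 11. The share of subjects seen early looks large only because any symmetric spread puts about half of them before Week 52, many by a few days; exposure lost is the better measure, and it is 0.8% to 1.9%. If SAEs and AESIs occurred at 2% to 5% per year (an assumption; the protocol gives no rate), the expected number missed in the whole trial would be between 112/52 × 0.02 = 0.04 and 280/52 × 0.05 = 0.3. The study tests no hypothesis, and all arms share the window under observer-blind conduct, so no between-arm bias is shown.

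All of this stands, and it limits the weight of the point. It does not remove the mismatch: a site that follows the protocol exactly will stop asking about SAEs and AESIs before the endpoint period is over.

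Stronger readings are tempting, but the document does not support them:
- **That the final lock cuts subjects off.** Step 4 shows that it does not; collection ends at each subject's Visit 11.
- **That every subject seen early is affected.** Someone without a second dose falls short only if seen in about the first week of the window.
- **That the endpoint mixes 48 to 56 weeks of follow-up.** Events after Week 52 are outside it, so the range within the endpoint is 48 to 52 weeks.
- **That early attenders will be counted as event-free to Week 52.** Section 7.3.4.1 does not say how follow-up time is handled. That belongs in a SAP, and its absence here is no finding.

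**Conclusion.** The point holds, as a small defect in data collection. The SAE and AESI endpoints need 364 days of observation after the last dose, and the protocol guarantees 336 days for two-dose subjects. The shortfall is up to 28 days (7.7%) for a two-dose subject seen early and at most about 7 days for a subject without a second dose. It affects unrelated SAEs and non-serious AESIs.

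These limits follow from the protocol's own dates and need no assumption. The trial-wide figure of 112 to 280 subject-weeks (0.8% to 1.9%) rests on assumed visit-date distributions and on all 280 planned subjects completing. With descriptive analysis and a common window, the consequence is slight under-recording of late events. Sections 4.2.11, 7.2.1, 7.3.4.1 and 8.2 need to be brought into agreement.

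**What to change.** **Preferred.** Keep the ±4-week window for the Week 52 blood sample. Add to Sections 8.2 and 4.2.11 that any subject whose Visit 11 falls before Day 364 after the last dose is telephoned on or after Day 364, and before the final lock, for SAEs and AESIs. Align the reporting cut-off in Section 8.4 with that contact. The protocol already uses telephone follow-up of this kind for withdrawn subjects. The cost is one short call per early attender and a wording amendment. Made promptly after Day 364, the call falls within that subject's permitted Visit 11 window, which runs to Week 56.

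**Failing that.** Restate the endpoints in Section 7.2.1 and the analysis in Section 7.3.4.1 as SAEs and AESIs to Visit 11 (Week 48 to 56), and report actual follow-up time. This costs nothing in conduct but gives up the fixed 52-week period.

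**Less attractive.** A plus-only window (52 + 4 weeks) would also close the gap, but Visit 11 carries the Week 52 ELISA and FRNT samples. It would halve the window and move those samples late, to Week 54 on average if visits were spread evenly over Weeks 52 to 56.

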**4.2.12 Unscheduled visits**

Besides scheduled visits, additional visits may be conducted any time upon the request of subjects or their representatives or whenever deemed necessary by the investigator. The investigator will remind the subjects of this during their regular study visits and instruct them to immediately contact the investigator in the event of AEs. Unscheduled visits should not affect the schedules of regular visits. During unscheduled visits, tests can be done as necessary at the discretion of the investigator.

## **5. Subject selection and withdrawal criteria**

### **5.1 Inclusion criteria**

To be eligible for enrollment, individuals must meet all of the criteria described below.

- 1) Individuals who voluntarily decide to participate in this study and provide written informed consent:
  - Healthy male and female adult at the age of 19 to 50 years (Part A)
  - Healthy male and female adult at the age of 19 to 75 years (Part B)
- 2) Individuals who, after receiving detailed explanations about the study, voluntarily decide to participate in this study and provide written informed consent
- 3) Individuals who are available for all visit procedures including telephone visits during the study period

### **5.2 Exclusion criteria**

Individuals who meet any of the criteria described below will be excluded from enrollment.

- 1) COVID-19 positive based on RT-PCR using upper respiratory tract (oropharyngeal, nasopharyngeal) or lower respiratory tract (sputum) sampling or COVID-19 antibody (IgM and/or IgG) positive
- 2) History of SARS-CoV, MERS-CoV or SARS-CoV-2 infection
- 3) Increased risk of exposure to SARS-CoV-2 (e.g., healthcare workers in direct contact with patients with COVID-19)
- 4) History of vaccination against SARS-CoV, MERS-CoV, or SARS-CoV-2
- 5) Immune system disorders including immunodeficiency disease
- 6) Planned blood donation or transfusion during the study period
- 7) Planned administration of other vaccines from 4 weeks before the 1st dose to 4 weeks after the 2nd dose of the IP
- 8) Height and/or weight measurements at screening:
  - ① Body weight <40 kg or > 100 kg
  - ② Body mass index <18 kg/m^2 or > 30 kg/m^2
- 9) Clinically significant abnormalities in clinical laboratory test, ECGs and chest X-ray during screening in the opinion of the investigator (e.g., Wolff-Parkinson-White syndrome)

- 10) Any planned surgery during the study period
- 11) Fever ( $\geq 37.5^{\circ}\text{C}$ ) within 3 days prior to screening or serious acute (acute fever, cough, respiratory distress, chills, myalgia, headache, sore throat, anosmia, or ageusia) or chronic infection within 7 days prior to screening (requiring systemic antibiotics or antivirals)
- 12) Evidence or history of serious acute, chronic, or progressive disease (e.g., cancer, diabetes mellitus, chronic pulmonary disease, acquired immune deficiency syndrome (AIDS), blood dyscrasias, or immune system, urinary system, mental, musculoskeletal system, cardiovascular system, respiratory system, endocrine, nervous system, hepatobiliary system, renal disorders, etc.) which, in the opinion of the investigator, makes the individual ineligible for the study
- 13) Positive serum tests during screening [type B hepatitis, human immunodeficiency virus (HIV), type C hepatitis]
- 14) History of treatment with antipsychotics or opioid analgesic dependence within 6 months prior to IP dosing
- 15) History of severe allergic reactions (e.g., anaphylaxis, Guillain-Barré Syndrome) or severe hypersensitivity reactions to the IP or any of its components
- 16) History of therapy that might affect immunity: treatment with immunosuppressants or immune modifying drugs, anticancer therapy, or radiotherapy within 3 months prior to screening
- 17) History of systemic steroids (prednisone  $\geq 10\text{mg/day}$  for  $> 14$  consecutive days) within 3 months prior to screening. Topical, inhaled, and intranasal corticosteroids are allowed regardless of dose.
- 18) Past treatment within 3 months prior to screening, or planned treatment during the study period, with immunoglobulin or blood derivatives
- 19) Individual with thrombocytopenia or other coagulation disorders for whom intramuscular (IM) injections are contraindicated or individual who is on anticoagulant therapy\*  
\* Anticoagulant therapy: continuous use of anticoagulants such as coumarin/warfarin or new oral anticoagulants/antiplatelets
- 20) History of excessive alcohol consumption or drug addiction
- 21) Women of childbearing potential who do not agree to use medically allowed methods of contraception\* or to be heterosexually inactive until 60 days after the last dose of the IP  
\*Hormonal contraceptive, intrauterine device(IUD(intrauterine device) or IUS(intrauterine system)), tubal ligation, double-blocking method(condom for male and female, cervical cap or diaphragm, complex method such as contraceptive sponge), single-blocking method using spermicides
- 22) Pregnant or breastfeeding woman

- 23) Treatment with other IPs within 6 months prior to participation in this study
- 24) The investigator who is directly related to this study or sub-investigator/study coordinator who is supervised by investigator or their family member
- 25) Other reasons including medical reasons based on which the individual is considered to be ineligible for this study in the opinion of the investigator

